### Primary endpoint

The study hypothesis will be tested by a two-sided chi square test for independent proportions.

The hernia rate is calculated as a Kaplan-Meier estimate for the failure rate at the end of the observation period (1 year ± 1 month). The Kaplan-Meier estimate has the benefit of additionally taking into account the results of drop-out patients. For each hernia, the date of its first observation must be documented to provide a correct estimate. The date of hernia detected by ultrasound at a follow-up examination will be set to the examination date; this may lead to a slight over-estimation of the hernia rates in both groups.

Analyses will be performed according to the intention-to-treat principle. The consistency of the results will be tested by per-protocol analysis (sensitivity analysis).

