### Outcome measures

#### Primary outcome measure

The primary endpoint of the study is the frequency of incisional hernias 1 year postoperatively, as assessed by ultrasound examination.

An incisional hernia is defined as an ‘abdominal wall gap with or without bulging in the area of a postoperative scar perceptible or palpable by clinical examination or imaging’ according to the European Hernia Society. Incisional hernias will be classified according to their localization and size.

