### Statistical analysis

A planned analysis will be performed after all patients have completed their 1 year follow-up (primary endpoint). All data available until 1 year follow-up will be analyzed. Additional analyses will be conducted after completion of the 3 and 5 year follow-ups. It is intended to publish the 1 year result as well as the 3 and 5 year results in a peer-reviewed journal.

The statistical analysis of the primary endpoint has a confirmative character, whereas the secondary endpoints will be analyzed exploratively.

The description of the patient cohort with respect to demographic data and the baseline values of investigated parameters will take place as a whole as well as grouped by treatment group.

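### The confirmatory chi-square test and the Kaplan-Meier hernia rate are not tied to the same patients or the same quantity, so the p-value need not belong to the reported rates

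*Protocol article*

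**What the plan says.** All references are to the protocol article.

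- **Test.** Under Primary endpoint (Statistical analysis): "The study hypothesis will be tested by a two-sided chi square test for independent proportions".
- **Rate.** The same section continues: "The hernia rate is calculated as a Kaplan-Meier estimate for the failure rate at the end of the observation period", that end being 1 year ± 1 month. The reason given is: "The Kaplan-Meier estimate has the benefit of additionally taking into account the results of drop-out patients".
- **Dating.** "The date of hernia detected by ultrasound at a follow-up examination will be set to the examination date". The article expects this to bias the rates upward only slightly, in both groups.
- **Population.** "Analyses will be performed according to the intention-to-treat principle", with a per-protocol analysis as the consistency check.
- **Status.** Under Statistical analysis: "The statistical analysis of the primary endpoint has a confirmative character". Secondary endpoints are exploratory.
- **Planning.** Sample size calculation uses 19% versus 9.5%, 80% power and 5% alpha. It arrives at 212 per group (424), raised to 468 for 10% drop-out, without replacement of withdrawn patients.
- **Visits.** Study design lists day 2, discharge, 30 ± 10 days, 1 year ± 1 month, then 3 and 5 years.

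**The concern.** A chi-square test needs a yes or no for each patient in the table. A Kaplan-Meier estimate lets patients leave the risk set without a yes or no, and its variance is not that of a binomial proportion on the randomised n. The article fixes both for its only confirmatory comparison and does not link them. It does not say whether drop-outs are in the table or, if they are, with what status, and it names no test suited to Kaplan-Meier estimates.

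Two things are at stake. First, the p-value and the two published rates may describe different patients and quantities, and the choice between readings stays open until data are in hand. Second, the Kaplan-Meier rate depends on a censoring rule for hernia-free patients that the article does not give, although it does fix the event date and the time at which the curve is read.

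**Working it through.** **1. The plan's own figure.** With p1 = 0.19, p2 = 0.095, mean 0.1425, two-sided alpha 5%, power 80%, pooled variance and no continuity correction:

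n = [1.960·√(2·0.1425·0.8575) + 0.842·√(0.19·0.81 + 0.095·0.905)]² / 0.095² = (0.9689 + 0.4122)² / 0.009025 = 211.4, so 212 per group.

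This matches the article. The trial is sized as a plain two-proportion comparison among evaluable patients.

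**2. Chi-square among examined patients.** 468 × 0.9 = 421, or 210 to 211 per arm. Power by the same formula is 79.7% to 79.9% (80.7% in 200,000 simulated trials), and simulated type I error is 5.0%. This is valid if drop-out is non-informative. It leaves drop-outs out, whereas the stated rate is said to include them.

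**3. Kaplan-Meier rates entered with the randomised n.** Take 234 per arm, drop-out d, and no hernia seen before a drop-out. Each rate then carries information from 234(1−d) patients, but the test credits 234. The statistic is too large by 1/√(1−d), so

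type I error = 2·P(Z > 1.96·√(1−d)).

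| Drop-out | 1.96·√(1−d) | Type I error |
|---|---|---|
| 10% (planned) | 1.859 | 6.3% |
| 15% (assumed) | 1.807 | 7.1% |
| 20% (assumed) | 1.753 | 8.0% |

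Simulation agrees (6.3% at 10%, 8.0% at 20%).

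**4. Reading the curve at window end with individual visit dates.** The answer depends on where hernia-free patients are censored.

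- *Censored at window end.* Nobody is censored between the first and the last 1-year examination, so the estimate reduces to hernias / examined. A true 19% stays at about 19%.
- *Censored at their own visit, all visit dates distinct.* When r examined patients remain, the next visit multiplies survival by 1 − 1/r with probability p, so its expected factor is 1 − p/r. Over n examined patients the expected failure rate is 1 − Π(1 − p/r), r = 1 to n. With n = 211 this is 0.686 for p = 0.19 and 0.435 for p = 0.095. Simulations with visits spread evenly over 11 to 13 months gave 68% to 69% and 43% to 44%. Visits bunched around 12 months in a bell shape gave about 60% and 37%.

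The last few patients drive this: a hernia found at the latest visit takes the curve to 100%. The evenness of the spread and the own-visit censoring are both assumptions.

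**5. The reason given for Kaplan-Meier.** No visit is scheduled between 30 ± 10 days and 1 year ± 1 month. A patient lost in that gap with no hernia recorded leaves the risk set before the 1-year ultrasounds begin and does not change the estimate. A patient whose hernia was seen before loss does count. The benefit is real but limited to that second group.

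**The case against.** The strongest reply is that the sample size calculation shows what is meant: a chi-square test among examined patients, with 10% added for losses. That reading keeps its 5.0% error and about 80% power. If 1-year results are also placed at one common time and no hernia precedes a drop-out, Kaplan-Meier equals the examined proportion, and test and rate agree. All of this stands, and it limits the severity. It does not remove the conflict, because the article uses individual examination dates and justifies Kaplan-Meier by its use of drop-outs.

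A reader might infer more, but the document does not support it:

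- *The test is invalid whichever way it is read.* Step 2 shows that it is not.
- *A true null would be rejected in most trials.* Simulations of about 62% to 76% rejection need own-visit censoring and also Kaplan-Meier rates fed into the test with n = 234. The article states neither. With censoring at window end, reruns gave 6.0% and 6.8%.
- *Drop-outs are counted as hernia-free.* No text says so, and the sample size treats them as lost. That rule would test 17.1% versus 8.55% (0.9 × 19% and 0.9 × 9.5%). Its type I error rises only if drop-out differs between arms, for which the article gives no figure.
- *Kaplan-Meier gains nothing from drop-outs.* Hernias seen before loss do count.
- *Test and rate count different events.* The definition accepts a hernia "perceptible or palpable by clinical examination or imaging", and no sentence excludes one repaired before 1 year.
- *Missing-outcome sensitivity analyses are lacking.* An article may leave these to the full protocol or SAP, so their absence here is not a fault.

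**Conclusion.** The point holds as a mismatch written into the text of the only confirmatory analysis: the test is for simple proportions, the rate is a Kaplan-Meier estimate, and the treatment of drop-outs in the table is open. Its effect on the test is nil to modest at the planned 10% drop-out: type I error is 5.0% among examined patients (given non-informative drop-out) and about 6.3% if Kaplan-Meier rates are used with the randomised n. The values of 7.1% and 8.0% rest on assumed drop-out of 15% and 20%.

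The larger exposure is the reported rate. Under assumed even visits and own-visit censoring, 19% becomes about 69%, far beyond the slight bias the article predicts. Under window-end censoring there is no distortion. The article does not say which applies. This should be fixed, but it does not undermine the design or the sample size.

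**What to change.** Use one approach for both test and estimate.

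- **Option A, which fits the sample size as it stands.** Define a binary endpoint: any incisional hernia observed up to and including the 1-year visit. State which randomised patients enter the table and how a missing 1-year examination is handled. Test that proportion, and report it by arm with the difference and its confidence interval.
- **Option B.** Compare the 1-year Kaplan-Meier estimates by their difference with Greenwood variance, placing all 1-year examinations, with and without hernia, at one common nominal time. Simulated type I error is then about 5.1%.

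In either case, reword the claim about drop-outs so that it covers only hernias seen before loss. A missing-outcome sensitivity analysis, such as multiple imputation or a tipping point, is optional.

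The cost is a few sentences and minor programming, with N unchanged. The change should be made before the 1-year data are analysed. The article reports 55 patients randomised when it was written.

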### Sample size calculation

The ISSAAC study has shown a risk of 19% of developing an incisional hernia within one year using MonoMax® suture material and a long stitch technique for abdominal wall closure of a primary elective midline laparotomy [14]. The aim of this study is to demonstrate that the short stitch suture technique with MonoMax® will decrease the incisional hernia rate after 1 year by 50% compared with the long stitch technique (primary endpoint). Considering hernia rates of 19% and 9.5% in both groups, a total sample size of 424 patients (212 per group) will be necessary to detect this difference with a power of 80% and an alpha of 5%. Including a drop-out rate of 10%, a total of 468 patients will be randomized in the current study. Thus, each of the seven participating centers should recruit about 67 patients. To avoid center effects, a maximum of 200 patients may be recruited per center. Withdrawn patients will not be replaced.

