### Secondary endpoints

Secondary endpoints will be tabulated as frequencies and rates, or as means and standard deviations, as appropriate. Confidence intervals will be used when appropriate.

The two-sided chi square test for independent proportions will be used for proportion comparisons. The Kaplan-Meier method will also be used to calculate other rates to be analyzed. For each such event, the date of occurrence must be recorded. The two-sided *t* test for independent samples will be used for comparisons with continuous variables.

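### The confirmatory chi-square test and the Kaplan-Meier hernia rate are different statistics, and the rate as defined can be badly inflated by the spread of visit dates

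*Protocol article*

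**What the plan says.** In the protocol article, Primary outcome measure defines a simple frequency: "The primary endpoint of the study is the frequency of incisional hernias 1 year postoperatively, as assessed by ultrasound examination".

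Under Statistical analysis, Primary endpoint, the test is fixed: "The study hypothesis will be tested by a two-sided chi square test for independent proportions". The next paragraph defines the rate: "The hernia rate is calculated as a Kaplan-Meier estimate for the failure rate at the end of the observation period", that window being 1 year ± 1 month. The reason given is that "The Kaplan-Meier estimate has the benefit of additionally taking into account the results of drop-out patients". On dating: "The date of hernia detected by ultrasound at a follow-up examination will be set to the examination date". The authors expect this to overstate the rates only slightly. The same section calls for intention-to-treat analysis, with per-protocol as a sensitivity analysis.

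Secondary endpoints repeats the pairing. Proportions are compared by chi-square, and "The Kaplan-Meier method will also be used to calculate other rates to be analyzed".

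Sample size calculation assumes 19% versus 9.5%, 80% power, 5% alpha and 10% drop-out without replacement. This gives 424 patients, raised to 468.

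**The concern.** A chi-square test for proportions needs a count over a fixed denominator in each arm. A Kaplan-Meier failure rate has no such denominator and carries its own (Greenwood) variance. The stated merit of Kaplan-Meier is that it uses drop-outs' follow-up, which is exactly what the chi-square test cannot do. The article does not say which counts enter the test or how the p-value relates to the reported rates.

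A second difficulty lies in the rate itself. Hernias are dated at examinations scattered over two months, and the curve is read at the end of that window. If patients found hernia-free leave the risk set on their own examination day, few remain at risk near the end, and each late hernia produces a large step.

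The primary analysis is the trial's only confirmatory one. If the choice is left open, an analyst could make it after seeing results, and the published rates may not match the published p-value.

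**Working it through.** **1. The plan's own figure.** Inputs from Sample size calculation: p1 = 0.19, p2 = 0.095, mean 0.1425, two-sided 5%, 80% power.

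n = [1.960·√(2·0.1425·0.8575) + 0.8416·√(0.19·0.81 + 0.095·0.905)]² / 0.095² = (0.9689 + 0.4122)² / 0.009025 = 211.4, so 212 per group and 424 in total, as stated. Then 212 × 1.1 = 233.2, rounded up to 234 per group, gives 468. The planning basis is therefore a plain two-proportion test.

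**2. The same data, two p-values.** With 10% drop-out, 234 × 0.9 = 210.6 patients per arm are assessed.

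- Counts among assessed patients: z = 0.095 / √(0.1425·0.8575·2/210.6) = 2.79, p = 0.0053.
- Kaplan-Meier rates treated as proportions of 234: z = 0.095 / √(0.1425·0.8575·2/234) = 2.94, p = 0.0033.

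The second understates the variance. Its error rate is 2·[1 − Φ(1.96·√0.90)] = 6.3%.

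**3. Simulation, 234 per arm, 10% drop-out, all 1-year visits at one nominal time.** Assumed: drop-out independent of hernia; 0% or 30% of hernias found before the 1-year visit.

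| Analysis | Type I error | Power, 19% v 9.5% |
|---|---|---|
| Chi-square, assessed patients | 5.1-5.3% | 80-81% |
| Kaplan-Meier rates in a chi-square with n = 234 | about 6.5% | 82-84% |
| Kaplan-Meier difference, Greenwood variance | 5.2-5.5% | 80-82% |

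With 30% of hernias found early, the proportion among assessed patients is 19.3% against a Kaplan-Meier 19.0%, a small gap.

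**4. The denominator matters.** If drop-outs are counted as hernia-free among all randomised, the test compares about 17.1% with 8.6% while Kaplan-Meier reports 19% and 9.5%. Its type I error is about 5% with equal drop-out but 7-9% with 5% versus 15% (assumed).

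**5. The Kaplan-Meier rate with actual examination dates.** Assume that hernia-free patients are censored at their own visit, all dates differ, and hernia is unrelated to the visit date. With 211 patients per arm entering the window, expected survival at its end is the product over r = 1 to 211 of (1 − p/r):

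- p = 0.19: product 0.314, reported rate 68.6%.
- p = 0.095: product 0.565, reported rate 43.5%.

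Read mid-window (r = 106 to 211 only), the rates are 12.4% and 6.4%. Simulation with visits uniform over months 11 to 13 agrees: 68.7% (SD 19 points) and 43.1% at 13 months, 12.4% and 6.3% at 12 months. Other simulated visit patterns gave means of 60-66% for a true 19%.

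If hernia-free patients are instead followed to the window end, with hernia dates unchanged, the rate is 19% and the Greenwood test has about 81% power.

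**6. Greenwood errors alone.** With own-visit censoring and spread dates, the Greenwood test rejected in about 14-31% of null trials, depending on the visit pattern and on how arms whose curve reaches zero are handled.

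**The case against.** The strongest reply is that endpoint, sample size and test already agree. The endpoint is a frequency, the 212 per group is a chi-square calculation, and the test is named in its own sentence. Kaplan-Meier then only describes how the rate is reported. Nothing says that Kaplan-Meier rates are multiplied by the randomised n, and denominators and censoring rules commonly sit in a fuller protocol or analysis plan. Since the authors expect only slight over-estimation, they cannot have meant a curve that turns 19% into 69%.

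Much of this stands. The natural reading gives a valid test. What it does not remove is that the article states both elements, and they conflict. The p-value does not belong to the rate as defined, and the reading point and dating rule are written down, so this is more than omitted detail.

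Stronger readings are tempting but unsupported:

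- A reader might infer that the confirmatory test is invalid. It is not when run on counts of assessed patients.
- A reader might infer false-positive rates of 63-75%. These need Kaplan-Meier rates in the chi-square, own-visit censoring and a reading at the window end, all at once; the article states neither the first nor the second.
- A reader might infer that the 80% power fails for a Kaplan-Meier comparison. It holds with nominal or window-end dating; the figure of about 40% arises only under own-visit censoring.

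**Conclusion.** The point holds as a mismatch between the confirmatory test and the defined rate, in the current text of the only confirmatory analysis. For the test the consequence is modest: about 5% error on assessed counts, and about 6-7% if Kaplan-Meier rates are entered with the randomised n, at 10% drop-out and a common visit date. The stated 80% power is not wrong.

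The larger risk is to the reported rate. Under own-visit censoring, which is ordinary practice but is assumed here, a rate read at the end of the window would be about 60-69% for a true 19%, far from a slight over-estimation. Under follow-up to the window end there is no such distortion. A published result should not depend on which of these the analyst happens to choose.

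**What to change.** Replace the Primary endpoint wording with one paragraph:

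- Define the primary outcome as incisional hernia yes/no at the nominal 1-year visit.
- Take the per-arm rates, the risk difference with 95% CI and the chi-square p-value from the same counts, among patients with a 1-year assessment or a hernia documented before it.
- State a sensitivity analysis for missing ultrasound, so that the intention-to-treat claim has a defined treatment of drop-outs.
- Show Kaplan-Meier as supportive, with all 1-year examinations assigned to one nominal time.

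If Kaplan-Meier is kept as the primary estimate, use the nominal visit time together with a Greenwood-based test of the difference; Greenwood errors alone are not enough. Pair test and estimate in the same way for the rates under Secondary endpoints.

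The cost is one paragraph before unblinding, with no extra patients or data, since either coherent pairing keeps about 80% power at the current size. The downside of the preferred option is that the primary test does not use the partial follow-up of drop-outs.

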### Secondary endpoints

Secondary endpoints will be tabulated as frequencies and rates, or as means and standard deviations, as appropriate. Confidence intervals will be used when appropriate.

The two-sided chi square test for independent proportions will be used for proportion comparisons. The Kaplan-Meier method will also be used to calculate other rates to be analyzed. For each such event, the date of occurrence must be recorded. The two-sided *t* test for independent samples will be used for comparisons with continuous variables.

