## Methods

### Study design

The Effect of Suture Technique on the Occurrence of Incisional Hernia (ESTOIH) study is a prospective, international, multicenter, double-blinded, randomized controlled trial, aimed at evaluating the efficacy of the short stitch suture technique using an elastic, extra-long term absorbable monofilament suture (MonoMax®) after primary median laparotomy, in comparison with the long stitch suture technique.

In total, 468 patients will be enrolled in seven centers located in Germany and Austria. Patients will be randomly allocated to receive either the short or the long stitch suture technique for abdominal wall closure in a 1:1 ratio. The surgical procedure used to close the abdomen will be standardized in both suture technique groups and the participating centers will be trained in the different suture techniques.

After the operative procedure, the investigator will examine the patients on the second day after surgery, on the day of discharge, and at 30 days ±10 days, 1 year ±1 month, 3 years ±3 months and 5 years ±3 months postoperatively. Patients and observers performing the follow-up visits will be unaware of the suture technique (double-blinded) used. The study will last 5 years for each patient (Figures 1 and 2).

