### Participants

Patients at least 18 years of age undergoing an elective primary median laparotomy, with an incision length of ≥15 cm and an expected survival time longer than 1 year, and with an American Society of Anesthesiologists (ASA) status of I to III are eligible for this trial. After approval of the study protocol by the local ethics committee, patients will be screened consecutively for possible eligibility in the participating centers. All patients who seem to meet the in- and exclusion criteria will be asked whether they are willing to participate in the ESTOIH study and will be informed about the purpose of the trial. Written informed consent has to be obtained from each enrolled patient before the operation.

Exclusion criteria are:Emergency surgery,Body mass index ≥30 kg/m^2^,Pancreatic tumor patients,Patients who will be operated on owing to an abdominal aortic aneurysm,Peritonitis,Coagulopathy,Current immunosuppressive therapy (more than 40 mg of a corticoid per day or azathioprine),Chemotherapy within 2 weeks before operation,Radiotherapy of the abdomen within 6 weeks before operation,Pregnant women,Severe neurologic and psychiatric disease,Lack of compliance.

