Long term complications include the frequency of incisional hernias after 3 and 5 years after surgery, ad detected by ultrasound examination. Furthermore, wound infections according to CDC classification 1 year postoperatively and wound healing complications occurring within 1 year after surgery will be investigated.

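### Kaplan-Meier with deaths handled as drop-outs would overstate the hernia frequency that patients experience at 3 and 5 years

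*Protocol article*

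**What the plan says.** All of this is in the protocol article.

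- **Endpoint.** Under Secondary outcome measures: "Long term complications include the frequency of incisional hernias after 3 and 5 years after surgery".
- **Estimator.** Under Secondary endpoints: "The Kaplan-Meier method will also be used to calculate other rates to be analyzed". The same section gives the test for proportions: "The two-sided chi square test for independent proportions will be used for proportion comparisons".
- **Patients who leave early.** Under Primary endpoint, the method is justified in these words: "The Kaplan-Meier estimate has the benefit of additionally taking into account the results of drop-out patients". Death is not mentioned as a separate reason for leaving.
- **Admitted bias.** Ultrasound-detected hernias are dated to the examination, and of this the section says "this may lead to a slight over-estimation of the hernia rates in both groups". No other upward bias is acknowledged.
- **Population and horizon.** Participants must have "an expected survival time longer than 1 year". Study design adds: "The study will last 5 years for each patient". The exclusions include "Chemotherapy within 2 weeks before operation", recent abdominal radiotherapy and pancreatic tumor, but not cancer as a class.

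**The concern.** A patient who has died can no longer develop a hernia. Kaplan-Meier with hernia as the event censors that patient, and so treats the dead as if they would go on to develop hernias at the survivors' rate. One minus Kaplan-Meier then estimates the risk in a setting without death. The protocol declares no such target; it speaks of frequency, which is most naturally the share of patients who actually get a hernia.

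Deaths between years 1 and 5 are foreseeable here. Entry asks for little more than 1 year of expected survival, and the wording of the exclusions suggests that many cancer patients are eligible. Long-term outcome is a stated purpose of the trial, and the 3- and 5-year results are to be published. At stake are the absolute rates in those publications.

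**Working it through.** **The plan's own figure.** The protocol gives no 3- or 5-year rate to reproduce. Its sample size does reproduce. With 19% against 9.5%, two-sided 5%, 80% power and pooled variance (mean proportion 0.1425):

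n = [1.96·√(2·0.1425·0.8575) + 0.8416·√(0.19·0.81 + 0.095·0.905)]² / 0.095² = 211.4, so 212 per arm and 424 in total.

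This point does not touch that figure.

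**Inputs (long-stitch arm).**
- Hernia by 1 year: 19% (Sample size calculation).
- Hernia by 3 years: 19% × 1.6 = 30.4%, using the 60% increase from 12 to 36 months cited in the Discussion.
- After 3 years: the hazard of years 1 to 3 continues (assumption).
- Dead by 5 years: 10%, 30% or 50%, at a constant hazard and independent of hernia (assumption; the documents give no mortality).

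**Hazards per year.**
- Hernia, year 1: h₁ = −ln 0.81 = 0.2107.
- Hernia, later: h₂ = −ln(0.696/0.81)/2 = 0.0758.
- Death: m = −ln(1 − D)/5, which is 0.0211, 0.0713 and 0.1386 for D = 10%, 30% and 50%.

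**Formulas for T ≥ 1.**
- One minus Kaplan-Meier, deaths censored: 1 − exp[−h₁ − h₂(T − 1)].
- Cumulative incidence: h₁/(h₁+m)·[1 − e^−(h₁+m)] + e^−(h₁+m)·h₂/(h₂+m)·[1 − e^−(h₂+m)(T−1)].

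**Worked case, 30% dead, 5 years.** One minus Kaplan-Meier: 1 − exp(−0.2107 − 4·0.0758) = 40.2%. Cumulative incidence: 0.7471·(1 − 0.7542) + 0.7542·0.5153·0.4450 = 0.1836 + 0.1729 = 35.7%.

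| Dead by 5 years | 1 year: KM / cumulative incidence | 3 years | 5 years |
|---|---|---|---|
| 10% | 19.0 / 18.8 | 30.4 / 29.7 | 40.2 / 38.8 |
| 30% | 19.0 / 18.4 | 30.4 / 28.3 | 40.2 / 35.7 |
| 50% | 19.0 / 17.8 | 30.4 / 26.5 | 40.2 / 32.1 |

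The excess is 0.2 to 1.2 points at 1 year, 0.7 to 3.9 at 3 years and 1.4 to about 8 at 5 years.

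**Sensitivity to the late hazard.** If the 5-year rate without death is instead 30.4% × 1.1 = 33.4% (assumed), and survival at 1, 3 and 5 years runs from 98/94/90% down to 90/65/50%, cumulative incidence at 5 years is 32.6% down to 28.6%. The excess is then 0.9 to 4.8 points. At 3 years it is 0.6 to 3.5 points.

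**Effect of dating hernias to the visit.** A hernia then counts only if the patient is alive at the next visit, so each increment between visits is multiplied by survival to that visit. With the main inputs and 30% dead, survival is 0.931, 0.807 and 0.700:

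0.190·0.931 + 0.114·0.807 + 0.098·0.700 = 33.8%.

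The true value is 35.7% and Kaplan-Meier gives 40.2%. With 50% dead the same step gives 29.0%, against 32.1% and 40.2%. The visit-dated cumulative incidence reads low but lies closer to the truth than Kaplan-Meier.

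**The case against.** **The choice of target.** The trial compares two suture techniques, and hernia risk net of death is a legitimate target for that comparison. This stands for the between-arm contrast. A reader might infer that Kaplan-Meier makes arms with different mortality non-comparable. The reverse holds when death is independent of hernia. Give both arms the main hernia hazards and let 20% die in one and 40% in the other: Kaplan-Meier gives 40.2% in both, while cumulative incidence gives 37.2% and 34.0%. That is an apparent 3-point advantage for the arm with more deaths, and Gray's test would inherit it. The case for cumulative incidence is therefore confined to describing absolute frequency.

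**The cost saving per prevented hernia.** A reader might also infer that this is inflated. The documents do not show it. Secondary outcome measures gives neither a formula nor a time horizon, and if the measure divides a saving by hernias prevented, overstating the divisor would lower it.

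**Limited reach.** Secondary endpoints are exploratory, and proportions are compared by chi-square. With equal mortality in both arms the ratio between them hardly changes. The primary endpoint is barely affected. All of this stands and limits the weight of the point.

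**Scope.** The estimator sentence does not name hernia at 3 and 5 years, the handling of deaths is not spelled out, and a fuller protocol or SAP may settle both. The article nevertheless fixes Kaplan-Meier for further rates, and hernia at 3 and 5 years is the obvious candidate. Enrolment of cancer patients is likewise an inference from the exclusions. The gap between 1 year of required expected survival and 5 years of follow-up is stated outright.

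**Conclusion.** The point holds for the absolute 3- and 5-year hernia rates. If deaths are censored, the planned estimator exceeds the frequency actually experienced whenever patients die before they could develop a hernia, so the direction is certain. The size is not: it depends on assumed mortality, on the assumed hernia hazard after year 3, and on death being independent of hernia. At 10% mortality by 5 years the excess is small; at 50% it is material. Nothing here undermines the confirmatory 1-year analysis, the sample size or the relative comparison of the arms. It is a worthwhile and inexpensive improvement to the long-term reporting.

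**What to change.** In the analysis plan, report hernia at 3 and 5 years by arm as Aalen-Johansen cumulative incidence with death as a competing event, and show the number of deaths by arm at each time. Keep Kaplan-Meier or a cause-specific comparison alongside as the between-arm contrast net of death, and say which quantity each one estimates. Gray's test should not replace that contrast.

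No extra patients or visits are needed, but there are costs:

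- Dates of death must be collected; the article does not say that they are.
- Reported rates will be somewhat lower than under Kaplan-Meier.
- Because hernias are dated to the visit, a patient with an undetected hernia who dies before the next visit counts as dead without hernia. The estimate therefore reads slightly low (33.8% against 35.7% at 5 years with 30% dead), and the report should say so.
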